### 2.6 Prior to intervention

Prior to beginning the at-home intervention, all participants will be trained in the use of the IVR HMD tool in an in-person session. During the in-person onboarding session, an experimenter individually guides each participant through the main features and functionalities of the HMD tool. This includes demonstrating how to power the device on/off, recharge it, connect to Wi-Fi, calibrate the virtual environment, and access the intervention. Crucially, the experimenter also shows participants the exercises to perform (according to allocation) through video tutorials and has each participant complete a trial level directly with the HMD to ensure they are comfortable and proficient before starting the training independently. This hands-on, individualized guidance is essential to ensure that participants, many of whom may be new to VR technology, are fully confident and competent in using the device and accessing the training safely and effectively from home. Moreover, the participants are given an ad hoc user's manual in paper format that provides detailed information about the HMD operating mode and the activities to be carried out. In this preliminary session, the experimenter also makes agreements with each participant regarding the specific days on which the exercises should be performed during the 5 weeks of intervention. At the end of the session, a dedicated IVR HMD is delivered to each participant to perform the 5-week intervention at home. Throughout the intervention period, remote technical support is available upon request. Interventions are scheduled daily and continuously monitored through the telemedicine platform. The platform provides real-time tracking of whether participants have initiated and completed their assigned sessions. Should a participant miss a session, the system automatically notifies the experimenter, prompting proactive contact to reschedule the session for the immediate following day. This approach ensures that the prescribed frequency and dose of the intervention are maintained as closely as possible. However, if three consecutive exercise sessions are missed despite the experimenter's prompts, the participant's intervention is terminated.

### 2.7 Intervention

All interventions (i.e., MC-I, CO-I, AC-I) are implemented in IVR environment and will be administered and managed through telemedicine approach.

#### 2.7.1 Multi-component intervention

Multi-component intervention (MC-I) includes both a SCD-tailored cognitive training (3 sessions/week, each lasting about 30 min) and a health and lifestyle education program (1 session/week, each lasting about 20 min), for a total of 20 sessions during a consecutive 5-week period (Figure 2).

**Figure 2 F2:**
[figure not shown]
Temporal organization of the Multi-component intervention over the 5-week period.

##### 2.7.1.1 Cognitive training

The selection of the most appropriate cognitive activities to be trained was made on the basis of empirical findings showing that individuals with SCD, while performing normally on traditional neuropsychological tests, have objective deficits in specific and more demanding cognitive processes (e.g., long-term associative memory, short-term memory binding, spatial pattern separation) when compared with healthy individuals without SCD (De Simone et al., 2023b; Kormas et al., 2020; Markova et al., 2023). For example, difficulty remembering face-name associations is one of the most commonly reported memory difficulties in SCD that underlines a subtle deterioration of associative memory processes, as demonstrated in our recent paper (De Simone et al., 2023b). As such, training to enhance memory for face-name associations could be an important priority for ecologically relevant improvement in SCD. Accordingly, our IVR cognitive intervention was developed to enhance those specific processes that have been consistently found to be impaired in SCD. In particular, two different tasks were implemented in virtual real-like scenarios of daily living situations, which target the following cognitive processes, respectively: (1) long-term associative memory (i.e., the ability to learn and remember associations between previously unrelated items), (2) working memory conjunctive and relational binding (i.e., the ability to integrate multiple features within an object representation or to associate one item to its spatial or temporal context), and (3) spatial pattern separation (i.e. the ability to differentiate partially overlapping patterns of activation in order to retrieve one pattern as separate from others that are similar).

The temporal sequence of the activity to performed in each individual session of cognitive training is represented in Figure 3 and described in detail below:

1) *Welcome screen (about 1 min)*. Participants are greeted with a customized welcome screen before beginning the tasks. Participants are asked to rate their current state using visual analog scales (VAS) ranging from 0 (*not at all*) to 100 (*a lot*) for three questions: “*Do you feel good right now?,” “Do you feel motivated?,”* and “*Are you tired?.”* Participants then click the start button to begin the cognitive exercises.2) *Virtual Face Name Memory training—Part I (about 5 min)*. This first part of the virtual face-name memory training consists of two learning phases followed by an immediate names and occupations recognition test. At the beginning of the task, a series of 3D faces, each associated with a name and an occupation, are presented individually for 8 s (Figure 4A). Participants are asked to read aloud the name and occupation associated with each face in order to ensure that they are attending to the items. At the end of the series, this procedure is repeated for the second learning phase: the same set of face-name-occupation associations are presented again (in a different order) and participants are asked to read aloud the name and occupation for each face. Following the second learning phase, participants are shown the previously learned faces, one at a time, and asked to perform a three-alternative forced-choice recognition, selecting the correct name and occupation (target) from a lure (a name/occupation paired with a different face) and a distractor (a novel, unstudied name/occupation; Figures 4B, C).

**Figure 3 F3:**
[figure not shown]
Temporal organization of an individual session of cognitive training.

**Figure 4 F4:**
[figure not shown]
Virtual face-name memory training—part I. Example of the virtual face-name memory training—part I. **(A)** During the two learning phases, a series of 3D faces, each associated with a name and an occupation (e.g., name: Riccardo; occupation: biologist), are displayed for 8 s in sequence. Then **(B)** participants are shown the previously learned faces, one at a time, and **(C)** asked to perform a three-alternative forced-choice recognition to identify the correct name and occupation (Translation of the instructions in **(B)** “*Do you remember his name*?”).

Faces are balanced for sex (females and males) and age (young adults and seniors) within each training session. The number of face-name-occupation associations to be learned and subsequently recalled progressively increases based on the participant's performance. All participants start with 5 face-name-occupation associations in the first training session (Day 1). The number of associations increases by one in subsequent sessions, up to a maximum of 20, after achieving at least 70% accuracy in the name delayed cued-recall task described in the “*Virtual Face Name Memory training—Part II”* section.

3) *Virtual Object Location Memory training (about 12 min)*. Virtual object location memory training consists of two tasks of increasing difficulty: a change-detection task (levels of difficulty from 1 to 3) and a yes/no recognition *plus* location memory task (levels of difficulty from 4 to 12). In both tasks, the scenario consists of a room containing several everyday objects in different spatial locations. During the study phase, participants are asked to carefully observe the scene at 180° and memorize the objects and their spatial locations. After a 13-s exposure, the room disappears. Following a 10-s blank (retention interval), the test phase is administered in change detection or yes/no recognition test format. Specifically:

- For the change-detection task, the room reappears with: (1) same objects in the same positions (no-change condition), (2) same objects in different positions (position-change condition), or (3) different objects in the same positions (object-change condition). Participants are asked to respond Yes or No to indicate whether the items and their locations in the study and test phases are the same or different. Participants who correctly identify a change are asked to click on the altered objects or locations to specify the change (Figure 5);- For the yes/no recognition *plus* location memory task, the room reappears, and a series of everyday 3D objects are presented individually in front of participants. The series includes items presented in the study phase (targets), new item not previously seen (foils), and new items that are perceptually similar to those seen during the study phase, but not identical (lures). For each stimulus, participants are required first to perform a yes/no recognition, indicating whether the presented item is a studied object (target) or an unstudied one (foil or lure). Then, once an object is correctly recognized as target, participants are asked to drag it to its remembered location (localization memory; Figure 6).

**Figure 5 F5:**
[figure not shown]
Virtual object-location memory training—change detection task. Example of the virtual object-location memory training—change detection task. **(A)** Participants are presented with a virtual living room containing 3D objects in specific spatial configurations for 13 s. **(B)** The scene is then occluded by a black panel for 10 s. **(C)** Subsequently, the living room reappears, either with the same or a modified object-location arrangement. Participants respond “Yes” or “No” to indicate whether any changes were detected (Translation of the instructions in **(C)** “*Have you noticed any differences?*”). **(D)** If a change is correctly identified, participants are prompted to select the altered objects or locations (Translation of the instructions in **(D)** “*Can you indicate which items have changed?*”).

**Figure 6 F6:**
[figure not shown]
Virtual object-location memory training—yes/no recognition *plus* location memory task. Example of the virtual object-location memory training—yes/no recognition plus location memory task. **(A)** Participants are presented with a virtual living room containing 3D objects in specific spatial configurations for 13 s. **(B)** The scene is then occluded by a black panel for 10 s. **(C)** Subsequently, individual 3D objects are presented and participants are required to perform a yes/no recognition, indicating whether the presented item is a studied or an unstudied object (Translation of the instructions in **(C)** “*Was this object present in the scene?*”). **(D)** If the object is correctly recognized, participants are prompted to localize it by clicking on the corresponding yellow cylinder representing its original location (Translation of the instructions in **(D)** “*Can you indicate where it was located?*”).

The Virtual Object Location Memory training comprises 12 levels of difficulty, each consisting of six different trials. Task difficulty adaptively increases from Level 1 to Level 12 based on participants' performance. This progression involves varying the task type (change-detection: levels 1–3; yes/no recognition plus location memory: levels 4–12) and the number of objects presented (change-detection: 3–5 items; yes/no recognition plus location memory: 3–11 items). All participants start at the easiest Level 1. After two consecutive successful trials (no errors), they advance to the next level.

4) *Virtual Face Name Memory training—Part II (about 8 min)*. The second part of the virtual face-name memory training assesses delayed cued-recall and recognition of the previously studied face-name-occupation associations. Specifically, previously studied faces are presented individually; for each stimulus, participants are asked to perform the following tasks:

(1) Name delayed cued-recall: participants are asked to recall the associated name; responses are provided using a virtual keyboard (Figures 7A, B). (2) Name recognition: for names not correctly recalled, participants perform a three-alternative forced-choice recognition task, selecting the correct name (target) from a novel name (distractor) and a lure (a name paired with a different face; Figure 7C). (3) Occupation Delayed Cued-Recall: participants are asked to recall the associated occupation; responses are provided by using a virtual keyboard. (4) Occupation Recognition: for occupations not correctly recalled, participants perform a three-alternative forced-choice recognition task, selecting the correct occupation (target) from a novel occupation (distractor) and a lure (an occupation paired with a different face).

5) *Final screen (about 1 min)*. The intervention concludes with a final screen. Participants are asked to rate their experience using VAS ranging from 0 (not at all) to 100 (a lot) for three questions: “*Did you experience any discomfort while using the system?,” “How mentally fatiguing were these tasks?,”* and “*How satisfied are you with your performance?.”*

**Figure 7 F7:**
[figure not shown]
Virtual face-name memory training (part II). Example of the virtual face-name memory training Part II. **(A)** Previously studied faces are presented individually. **(B)** Participants are asked to recall the name associated with each face using a virtual keyboard (name delayed cued-recall). **(C)** For incorrect recalls, participants perform a three-alternative forced-choice recognition task (name recognition).

##### 2.7.1.2 Health and lifestyle education program

The health and lifestyle education program consists of five key topics covered in immersive 360° VR videos featuring experts in the field. These videos aim to increase awareness and knowledge of the various health conditions associated with an increased risk of cognitive decline and dementia, empowering participants to develop healthier lifestyles (e.g., encourage healthy dietary habits, incorporate regular physical activity into daily routine, reduce sedentary behavior). The topics that are covered include (1) how aging affects cognition and the brain; (2) modifiable medical risk factors for cognitive decline and dementia, including weight, cholesterol, diabetes, hypertension, and sleep disturbance, as well as modifiable lifestyle risk factors, such as smoking, stress, physical activity, nutrition, and social and cognitive engagement; the protective effect of (3) Mediterranean diet and (4) regular physical and cognitive activities against cognitive impairments and dementia. To induce greater participant engagement, we recorded immersive 360° VR videos with three experts in the field (i.e., a geriatric doctor, a neuropsychologist and a nutritional biologist); the videos were implemented in the HMD. In this way, we could induce sense of presence, giving the participants the illusory sensation to be physically present in the scenario. In addition, to make the educational experience more engaging, interactive questions were implemented into immersive videos.

#### 2.7.2 Cognitive-only intervention

Cognitive-only intervention (CO-I) includes the SCD-tailored cognitive IVR training (3 sessions/week, each lasting about 30 min) and 5 sessions of active control of the education program (1 session/week, each lasting about 20 min). In this latter, participants will view immersive 360° VR educational videos on non-health-related topics (i.e., science and history) and answer specific questions about their content. This serves as a control for the educational component of the MC-I.

#### 2.7.3 Active control intervention

Active control intervention (AC-I) includes an active cognitive control, which serves as a placebo-like condition for the experimental SCD-tailored cognitive IVR training (included in both the MC-I and CO-I interventions). It also incorporates the same educational active control as used in the CO-I intervention.

In the active cognitive control, participants are asked to virtually carry out simple actions within the same virtual environment as those performed in the SCD-tailored cognitive IVR training. However, they have to follow prearranged instructions requiring minimal cognitive processing, typically involving simple step-by-step instructions or repetitive actions. For example, in the *Virtual Face Name Memory* active control, participants are shown the same stimuli (face-name-occupation associations) but are required to execute simple tasks that do not involve memory abilities (e.g., reading aloud the names and occupations associated with the presented faces, judging the pleasantness of faces, judging whether the name is appropriate for the face). Similarly, for the *Virtual Object Location Memory* active control, participants are immersed in the identical scenario as the experimental condition (a room containing several everyday objects in different spatial locations) but are required to perform simple tasks, such as counting the number of objects present in the virtual room. Frequency and duration are identical to those of the CO-I and MC-I conditions.

### 2.8 IVR and TM apparatus

Virtual stimuli, objects and environment were designed using 3DS Max 2022 (Autodesk, Inc.) and Unity 2022.3.5f1 game engine software, respectively. Two distinct virtual environments were developed and implemented. Specifically, for the *Virtual Face Name Memory training*, a minimalist virtual environment was created, characterized by a darkened spatial volume. A single, centrally positioned cylindrical column, illuminated by a focused spotlight, acts as the primary visual element. Facial stimuli, presented sequentially for 8-s intervals, were displayed at the top of the column. The 3D facial models were generated by adapting models of the Microsoft Rocketbox avatar library. For the *Virtual Object Location Memory training*, the virtual environment consists in a large living room with a centrally located table and a series of empty shelving units attached to the front wall. Within these shelves, a varying number of 3D objects are presented based on task difficulty. These 3D objects were designed and optimized using Autodesk 3ds Max 2022.

The tasks were programmed in Unity 2022.3.5f1 and built for the Meta Quest 2 head-mounted display (HMD), with a resolution of 1,832 × 1,920 pixels per eye, a refresh rate of 72 Hz and 6 degrees of freedom (DoF). An intuitive interaction modality was implemented using the Oculus Touch controller, combined with custom Unity C# scripts, enabling ray-cast object selection and trigger-based interaction. Immersive 360° VR videos for *health and lifestyle education program* were recorded using an Insta 360 X4, which captures with 25 fps with 8K resolution in 360° mode.

To remotely control and manage the HMD devices and task sequences, a dedicated telemedicine platform was developed, consisting of a web app developed in C# and implemented with Unity 2022.3.5f1 game engine software. The platform features a dedicated interface allowing the experimenter to remotely schedule daily exercise sessions for each participant, according to their assigned condition. Beyond scheduling, the platform provides real-time tracking of whether participants have initiated and completed their assigned sessions. Should a participant miss a session, the system automatically notifies the experimenter, prompting proactive contact to reschedule the session for the immediate following day. Furthermore, the web app generates detailed performance data from each VR session, offering the experimenter a comprehensive overview through quantitative metrics such as accuracy rates, number of errors, and response times. This integrated system ensures the experimenter can maintain an indirect yet significant control over the participant's experience, thereby guaranteeing adherence to the study protocol and offering valuable quantitative feedback on performance, all while facilitating remote oversight.

### 2.9 Planned statistical analysis

Statistical analyses that will be applied to the whole dataset of outcome measures include descriptive statistics (e.g., means, standard deviations, frequencies) and graphical exploratory data analytic techniques (e.g., residual plots, normal Q-Q plots) that will be performed to describe distributions of the data, to identify potential outliers and missing values, and to check for the possible violation of assumptions necessary for the planned statistical methods. Between-group differences in demographic (i.e., age, education) and screening neuropsychological test performance will be assessed using parametric (i.e., one-way analysis of variance—ANOVA) or non-parametric tests (i.e., Kruskal-Wallis) when appropriate. Chi-square test will be used to assess differences in sex distribution among groups. If data will be of normal distribution, possible between-group differences (MC-I group vs. CO-I group vs. AC-I group) in outcome measures at T0 and T1 will be analyzed using either repeated measures ANOVA or a similar repeated measures statistical technique such as linear mixed models. If linear model assumptions will be severely violated, an analogous non-linear repeated measures statistical approach will be used. In this case, variable transformation may be performed, if appropriate.

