In light of the foregoing, this study aims to evaluate the effectiveness of an immersive virtual-reality (IVR) and telemedicine-based multi-component intervention, combining cognitive training and a health and lifestyle education program, on objective and subjective cognitive function, psychiatric symptoms, quality of life and brain connectivity in older adults at high-risk for cognitive decline and dementia (i.e., SCD). The primary objective is to determine whether the multi-component intervention, when compared to an active control condition, leads to significant post-intervention gains in objective cognitive functioning, and whether these gains are greater than those induced by a cognitive-only condition. The secondary objectives are: (1) to assess the transfer effect of the intervention on self-perceived cognitive functioning, psychiatric symptoms and quality of life; (2) to assess intervention-induced changes in whole-brain functional connectivity, as highlighted by resting state-fMRI images; (3) to assess user compliance with telemedicine approach combined with IVR. Exploratory objectives include: (1) investigating potential moderators of intervention efficacy (e.g., demographics, cognitive reserve, SCD severity, lifestyle and dementia risk factors); and (2) evaluating hypotheses regarding neuroimaging results and their association with behavioral data (e.g., correlation between behavioral and imaging data, association between post-training brain changes and participants' characteristics, and whether intervention-induced improvements rely on specialized brain areas or depend on compensatory responses from other regions).

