## 2 Methods/design

### 2.1 Study design

This 5-week randomized controlled trial (RCT) use a double-blinded, three-parallel group design, guided in accordance with the Consolidated Standards of Reporting Trials (CONSORT) guidelines (Bennett, 2005). Following a screening phase to verify eligibility criteria through a comprehensive clinical and neuropsychological evaluation, and after obtaining informed consent, enrolled participants with SCD will undergo an in-person baseline assessment and a 3T MRI scan (where feasible) to collect clinical, neuropsychological, behavioral, and neuroimaging data prior to the intervention (T0). Then, using a stratified randomization method (ratio 1:1:1, taking age into account), participants will be allocated in a blinded fashion to one of the three experimental conditions:

(1) a multi-component intervention (MC-I), including SCD-tailored cognitive IVR training *plus* a health and lifestyle education program;(2) a cognitive-only intervention (CO-I), including SCD-tailored cognitive IVR training *plus* an active control for the education program;(3) an active control intervention (AC-I), including active controls for both cognitive training and education program.

The active control for the cognitive training (in the AC-I condition) involves IVR tasks mirroring the experimental training's structure but with very low cognitive demands. The active control for the education program (in both CO-I and AC-I conditions) consists of educational videos on topics unrelated to dementia and cognitive decline prevention. A detailed description of the interventions is provided in paragraph 2.7.

All three groups will receive 20 training sessions (4 sessions per week, each lasting about 30 min) over a period of 5 consecutive weeks. Participants will complete their respective interventions at home using virtual reality head-mounted displays (HMD) remotely controlled and monitored in real-time via a dedicated telemedicine platform. Prior to the intervention, all participants will receive in-person training on the use of HMD tool. Within 48 h and 1 week of completing the 5-week intervention, participants will return respectively for a post-intervention 3T MRI scan (where feasible) and an in-person evaluation, in order to collect post-training clinical, behavioral, neuropsychological and neuroimaging outcome measures (T1). A study flowchart is provided in Figure 1.

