### 2.3 Sample size calculation

To estimate the appropriate sample size, the G^*^Power program was used. Considering an effect size of 0.37 obtained in a recent meta-analysis on cognitive intervention in SCD (Sheng et al., 2020), a power of 0.8 and an alpha of *p* < 0.05, we applied repeated measurements of multivariate analysis of variance (three groups: MC-I group, CO-I group, AC-I group; two measurements: pre-intervention and post-intervention) for analysis. The appropriate sample size was determined to be 74. Therefore, each of the three experimental groups requires at least 25 participants.

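### The planned pre/post repeated-measures comparison treats T0 as a response and names no T0 or age covariate; it is valid, but baseline adjustment would give more precise arm contrasts

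*Protocol article*

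**What the plan says.** Section 2.9 compares the three arms "in outcome measures at T0 and T1", and these differences "will be analyzed using either repeated measures ANOVA or a similar repeated measures statistical technique such as linear mixed models". A non-linear analogue is allowed if assumptions are severely violated. The choice between ANOVA and mixed model is left open, and no covariate is named under either.

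Section 2.3 sizes the trial on the same kind of model: "we applied repeated measurements of multivariate analysis of variance", with three groups, two measurements and no covariate.

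Section 2.1 places the T0 assessment before allocation, which is then made "using a stratified randomization method (ratio 1:1:1, taking age into account". Age returns in two places only. Section 2.9 lists it among baseline comparisons: "Between-group differences in demographic (i.e., age, education) and screening neuropsychological test performance will be assessed". The Introduction includes demographics in an exploratory aim: "investigating potential moderators of intervention efficacy (e.g., demographics, cognitive reserve, SCD severity, lifestyle and dementia risk factors". It is not named as a term in the efficacy model.

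The Introduction sets two comparisons for the primary objective: MC-I against AC-I and MC-I against CO-I, both on post-intervention gains in objective cognition.

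**The concern.** T0 precedes randomisation, so any difference between arms at T0 is due to chance. The T0 score is then best used to explain variation in T1. As a second response, it makes the group-by-time contrast subtract the whole of T0, as if T1 tracked T0 one for one. When rho is below 1 (with similar SDs at the two visits), that over-corrects chance imbalance and adds noise.

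With 25 participants per arm and two pairwise contrasts to estimate, one of them between arms that differ only in the education component, lost precision matters. The T0 scores and ages will be collected anyway. Leaving the stratification factor out of the model also means that the standard error does not credit the balance that stratification creates; this makes inference conservative, not invalid.

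**Working it through.** **Inputs.** From the article: three arms, 25 per arm, 75 in total, two measurements, power 0.8, two-sided alpha taken as 0.05, effect size 0.37 (section 2.3). Not in the article: the T0-T1 correlation rho, assumed here from 0.3 to 0.9, and any correlation between age and outcome.

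**Step 1: the plan's own figure.** Section 2.3 bases its calculation on this input: "Considering an effect size of 0.37 obtained in a recent meta-analysis on cognitive intervention in SCD". Reading 0.37 as the effect size f of the group-by-time test, with noncentrality N × 0.37² and degrees of freedom 2 and N - 3, power is 0.797 at N = 73, 0.803 at N = 74 and 0.809 at N = 75. So N = 74 reproduces. Reading 0.37 as d (f = 0.185) with an assumed rho of 0.5 gives noncentrality N × 0.185² × 2/(1 - 0.5) = N × 0.37², hence 74 again. The stated sample size is not in error on this point.

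**Step 2: what the planned test is.** With two time points and complete pairs, the group-by-time contrast is the difference between arms in mean (T1 - T0). A mixed model with free T0 means gives the same contrast. With a common SD s at both visits:

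- change score: variance per participant = 2(1 - rho)s²
- ANCOVA on T0: variance per participant = (1 - rho²)s²
- ratio = (1 - rho²)/[2(1 - rho)] = (1 + rho)/2, so the saving is (1 - rho)/2

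**Step 3: size by assumed rho.** The standard-error saving is 1 - √[(1 + rho)/2].

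| rho (assumed) | Variance ratio | Variance saved | SE saved | Change-score N matching 75 with ANCOVA |
|---|---|---|---|---|
| 0.3 | 0.65 | 35% | 19.4% | 115 |
| 0.5 | 0.75 | 25% | 13.4% | 100 |
| 0.6 | 0.80 | 20% | 10.6% | 94 |
| 0.7 | 0.85 | 15% | 7.8% | 88 |
| 0.8 | 0.90 | 10% | 5.1% | 83 |
| 0.9 | 0.95 | 5% | 2.5% | 79 |

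The last column is 75 divided by the variance ratio. Simulation at 25 per arm (20,000 runs) gave variance ratios of 0.767 at rho 0.5 and 0.911 at rho 0.8, that is, savings of 23% and 9%. Estimating the T0 slope costs only a little of the theoretical gain.

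**Step 4: detectable pairwise difference.** At 80% power with 25 against 25 and 72 degrees of freedom, the detectable difference is about (1.993 + 0.847) = 2.84 times the standard error √(2 × variance/25), in units of s.

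- rho 0.5: 2.84 × √(2 × 1.00/25) = 0.80 for change; 2.84 × √(2 × 0.75/25) = 0.70 for ANCOVA
- rho 0.7: 2.84 × √(2 × 0.60/25) = 0.62 for change; 2.84 × √(2 × 0.51/25) = 0.57 for ANCOVA
- rho 0.8: 2.84 × √(2 × 0.40/25) = 0.51 for change; 2.84 × √(2 × 0.36/25) = 0.48 for ANCOVA

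The small-sample cost of the T0 slope, a variance factor of about 1 + 1/70, multiplies the ANCOVA figures by about 1.007 (for example 0.574 becomes 0.578).

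**Step 5: omnibus power.** If 0.37 is f for the change score, power at N = 75 moves from 0.81 to about 0.91 (rho 0.5), 0.87 (rho 0.7) or 0.85 (rho 0.8), with the small-sample factor included.

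**Step 6: age.** Adjustment removes about r² of the residual variance, where r is the partial correlation of age with T1 given T0: 1%, 4% or 9% for an assumed r of 0.1, 0.2 or 0.3. The article gives no basis for choosing among these.

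**The case against.** The strongest reply is that nothing here is wrong. In a randomised trial the group-by-time test is valid and unbiased, it matches the sizing model, and N = 74 reproduces. The article is condensed, and covariates are often left to an analysis plan, which is not shown here. All of that stands, and it limits the point to efficiency and specification. It does not remove it: placing T0 among the responses is a stated choice, repeated in section 2.3.

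A reader might infer several stronger things that the article does not support:

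- **That the analysis is fixed as a repeated-measures ANOVA.** Section 2.9 also allows linear mixed models, and one with a common T0 mean would recover the efficiency. One with free T0 means would not, and the text does not say which is meant.
- **That T0 and age will be excluded.** No covariate is named, but no exclusion is stated.
- **That a known share of precision, such as 10-25%, is lost.** That range is a variance figure for an assumed rho of 0.8 to 0.5; the standard-error equivalent is about 5-13%.
- **That a group main effect averaged over T0 and T1 could serve as the treatment test.** The objective is framed as post-intervention gains, which points to group by time.
- **That the parallel FNAME-12 form at T1 lowers rho, or that age adds a material gain.** Neither has a figure behind it. Change scores and T0 adjustment already absorb much of any stable age effect.

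**Conclusion.** The point holds as an improvement worth making, not as an error or contradiction. Under either listed technique, unless the mixed model constrains the T0 means to be equal, the planned contrast is a change-score comparison. T0 adjustment lowers its variance by (1 - rho)/2 for any rho below 1. The size rests wholly on the assumed rho: 25% at 0.5, 15% at 0.7 and 10% at 0.8. The formula assumes similar SDs at T0 and T1 and a linear relation with a common slope. The algebra is certain; the size for this trial's tests is not. The added gain from age is likely small and is not quantified; the main reason to include it is that randomisation was stratified on it.

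**What to change.** In section 2.9, or in the analysis plan with a reference from section 2.9, state for each objective cognitive test:

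- The primary analysis is an ANCOVA of the T1 score on arm, adjusted for the T0 score of the same test and for age (the stratification factor). A mixed model with a common T0 mean across arms plus age is equivalent.
- The results reported are the adjusted MC-I minus AC-I and MC-I minus CO-I differences, each with a 95% CI.
- Arm differences in the outcomes at T0 are described, not tested.

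The cost is a sentence or two and about two degrees of freedom (72 to 70 with 75 participants). No data or participants are added. Section 2.3 should note that the sample size was calculated for the unadjusted repeated-measures model.
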